### Recruitment

The potentially eligible participants at the intervention center are estimated at 100, while those at the control center are estimated at 50. Those participants will be approached by an investigator in their training schools. The potential benefits of participating in this study will be explained to ascertain the participants’ interest.

### Assignment of interventions: allocation

#### Sequence generation

We have a potential risk of communication between participants in the intervention and control groups if they are in the same institution. To avoid this, participants in the control group will be selected only at HIMT while participants in the intervention group will be selected at FMBS. These two institutions are geographically distant and they organize their clinical internships in several hospitals at the same time.

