## Trial design

This will be a controlled study with two parallel arms in two centers (Fig. 1). Participants meeting the inclusion criteria will be divided into two groups (1:1): an intervention group (additional lectures associated with a clinical internship and listening sessions based on digital recordings of heart sounds) and a control group (additional lectures with a clinical internship). This study will take place over a six-month period, from the 1st September 2021 to the 1 March 2022 at the Faculty of Medicine and Biomedical Sciences of Yaoundé (FMBS) and at the Higher Institute of Medical Technologies (HIMT). The follow-up of participants from both groups and data collection will take place throughout the study.

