#### Clinical internship

Participants in the control group will be required to participate in their official clinical internship (internal medicine) also as planned by their training school. This internship will take place in all the hospitals in Yaoundé that are accredited by the HIMT and will start after the delivery of additional lectures, over a period of two months.

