### Sample size

The minimum sample size will be calculated on the basis of a comparison of the average knowledge progression between the two groups. The hypothesis is that participants in the intervention and control groups will have an average of 30 % correct answers in the pre-tests and a 50 % increase in the intervention group compared to 10 % in the control group in the post-tests, i.e., an expected difference of 40 % between the two groups. For a power of 80 %, a ratio of 1:1 per group and an alpha error of 5 %, the minimum sample size will be 46 participants (23 per arm) [16]. Given the high risk of a refusal to participate, absenteeism and loss of sight, the minimum sample size will be increased by 20 %, for a total of 56 participants.

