### Statistical methods

#### Statistical methods for primary and secondary outcomes

The use of statistical methods will be based essentially on the comparison of participants from the two groups according to defined outcomes. The average knowledge progression of participants in the intervention group will be compared against those in the control group using Student’s t-test if the variables follow the normal distribution or by a non-parametric test if not. The average skill progression and the average total progression in knowledge and skills (based on the total progression score) of the intervention group will be compared against those of the control group using a Student’s t-test if the variables follow the normal distribution or by a non-parametric test if not. The other continuous variables (the pre-test knowledge score, the pre-test skills score, the pre-test total score, the post-test knowledge score, the post-test skills score and the post-test total score.) will also be compared using parametric or non-parametric tests. The satisfaction of all participants (ordinal variable) will be analysed using a non-parametric test.

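### Arm and school are the same variable, so the planned comparison estimates school plus method, and its 5% alpha and 80% power apply to the method only if school has no effect on progression

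*Protocol article*

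**What the plan says.** Under Trial design the protocol article states: "This will be a controlled study with two parallel arms in two centers". Under Sequence generation it adds that "participants in the control group will be selected only at HIMT while participants in the intervention group will be selected at FMBS". The reason given is contamination: "We have a potential risk of communication between participants in the intervention and control groups if they are in the same institution". There is no randomisation, and concealment is marked as not applicable.

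The primary analysis (Statistical methods for primary and secondary outcomes) is made at student level: "The average knowledge progression of participants in the intervention group will be compared against those in the control group", by a t-test or a non-parametric substitute. No term for school is planned, and the section on additional analyses rules out anything further.

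The Sample size section says: "For a power of 80 %, a ratio of 1:1 per group and an alpha error of 5 %, the minimum sample size will be 46 participants". Each arm thus has 23 students. The total is then raised by 20% to 56, or 28 per arm.

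Several exposures between pre-test and post-test are organised by school. The FMBS internship uses hospitals accredited by FMBS. For controls, "This internship will take place in all the hospitals in Yaoundé that are accredited by the HIMT". The extra lectures are held at FMBS for one arm and at HIMT for the other. The section on concomitant care lets students use whatever teaching materials their own school's curriculum provides.

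**The concern.** The primary objective is the effect of the digitally supported teaching method, and the article's discussion looks ahead to its wider use. The planned contrast, however, is between FMBS students who had the listening sessions and HIMT students who did not. If one school's regular courses or internship raise scores more over two months than the other's, that difference enters the result in full. It can act in either direction, so it could produce a positive result without any method effect, or hide a real one.

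Because the two variables coincide, neither a larger sample nor a different model can separate them afterwards. A p-value below 0.05 would be read as evidence for the method at a 5% error rate that the design does not secure.

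**Working it through.** **1. The plan's own figure.** The Sample size section assumes "participants in the intervention and control groups will have an average of 30 % correct answers in the pre-tests", then increases of 50% and 10%. Read as percentage points, the post-test levels are 30 + 50 = 80% and 30 + 10 = 40%. A two-sided pooled two-proportion formula, with mean proportion 0.6, gives

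n = [1.96·√(2·0.6·0.4) + 0.842·√(0.8·0.2 + 0.4·0.6)]² / 0.40² = (1.358 + 0.532)² / 0.16 ≈ 22.3,

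which rounds up to 23 per arm, 46 in all. Then 46 × 1.2 = 55.2, rounded up to 56. So the stated figure reproduces on this reading. A comparison of means would also give 23 if the SD were about 0.48, but no SD is stated. Either way, students are treated as independent and nothing allows for school.

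**2. Degrees of freedom for school.** There are two schools and two arm means, which leaves 2 − 2 = 0 degrees of freedom for between-school variance. A school indicator equals the arm indicator, so it cannot be fitted beside it. This step needs no assumed figure.

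**3. What the change score removes.** Write a student's progression as method effect + school effect on gain + student error. A constant school gap present at both tests cancels in post minus pre. The school effect on gain does not cancel, and it is present or absent together with the method.

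**4. Illustration with a random school effect.** Let r be the ICC of progression by school. It is assumed, because the documents give none. With n students in each of two schools and total variance σ²:

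- true variance of the difference in means: 2σ²[r + (1 − r)/n]
- variance that the t-test estimates: 2σ²(1 − r)/n
- ratio: V = 1 + n·r/(1 − r)

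With no method effect, the true two-sided error is 2·P(T > t_crit/√V) on 2n − 2 degrees of freedom.

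| r (assumed) | V, n = 23 | error, n = 23 | V, n = 28 | error, n = 28 |
|---|---|---|---|---|
| 0 | 1.00 | 5.0% | 1.00 | 5.0% |
| 0.01 | 1.23 | 7.6% | 1.28 | 8.2% |
| 0.02 | 1.47 | 10.4% | 1.57 | 11.6% |
| 0.05 | 2.21 | 18.2% | 2.47 | 20.8% |
| 0.10 | 3.56 | 29.1% | 4.11 | 32.7% |

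Simulation with 100,000 trials per setting agreed to within about 0.4 percentage points.

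**5. The same point with a fixed school effect.** With two deliberately chosen schools, the effect may be treated as a fixed shift of d SD in progression. With no method effect, the t statistic has non-centrality d·√(n/2). A shift of 0.2 SD gives rejection rates of 10.2% (n = 23) and 11.4% (n = 28). A shift of 0.5 SD gives 38.2% and 45.1%. These shifts are also assumed.

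**The case against.** The allocation has a stated and sensible reason: students in one school talk to each other, and the recordings are portable. The article calls the study controlled and does not claim randomisation. Much is held alike between arms: the topics, format and length of the extra lectures, the length of the internship, and the tests. The change score also takes out stable baseline gaps. All of this stands, and it limits what may be concluded. But contamination would mostly dilute a difference, whereas a school effect on gain can bias it either way, and nothing held alike removes that effect.

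Several stronger readings are tempting but not supported:

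- *The t-test exceeds 5% error.* This is so only if the school effect on progression is not zero. No ICC is given, so the tables above are illustrations and not separate evidence.
- *Each arm is a whole school.* Each arm is about 28 volunteers, from an estimated 100 eligible at the intervention school and 50 at the control school.
- *The schools differ in admission standard, hospitals and supervisors.* Admission standards are not mentioned. Four hospitals are named for FMBS and none for HIMT, so hospitals and supervisors may overlap.
- *The study yields no evidence on the method.* A pre/post comparison with a non-equivalent control gives weak evidence that depends on assumptions, which is more than none.
- *Randomising within schools is a free remedy.* The costs are set out under the fix.

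**Conclusion.** The point holds. Arm and school coincide by design, the planned test cannot separate them, and no part of the article acknowledges this. That conclusion rests on the allocation rule alone. The stated 5% alpha and 80% power are valid for a test of the method only under a zero school effect on progression, an assumption that the trial's own data cannot check.

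The size of the departure is unknown. Over an assumed ICC of 0.01 to 0.10, the true type I error would run from 7.6% to 29.1% at 23 per arm and from 8.2% to 32.7% at 28 per arm. The higher figures at 28 show that more students per school do not help. What must be corrected is how the design is described and how the result is interpreted. The documents do not show that the whole design must be replaced.

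**What to change.** **Needed.** In the abstract, design section and conclusions, describe the study as a non-randomised comparison of two schools. In the Sample size section, state that the 5% alpha and 80% power assume no school effect on progression and are not properties of a test of the method. Report the difference in progression as *school plus method*, with no confirmatory claim for the method. This costs wording and an amendment to the ethics committee and registry. It needs no extra students.

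**To consider before recruitment.** Enrol at both schools and allocate within each, with school as a stratum and a model term. This removes the confounding, but it is a trade-off:

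- The multimedia package given to intervention students could be passed to classmates, which is the risk that the present allocation avoids.
- The blinding section rests participants' unawareness of their group on the separate schools, and this would be weakened.
- Dilution would cost power. If internship groups were allocated, clustering would too, so 46 to 56 students may not be enough.
- Listening sessions are now planned only at FMBS and the schools are far apart, so running them for both adds logistics.

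If these costs are judged too high, the wording changes suffice, with the narrower conclusion that they imply.

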#### Concealment mechanism

Not applicable.

#### Implementation 

All participants will be invited to take part in three additional lectures and a pre-test prior to their official clinical internships. SMS and phone calls will be used during clinical internships to follow up all participants. Participants in the intervention group will receive additional SMS reminders to encourage them to participate in the supervised listening sessions and to conduct their own listening sessions. Participants in the intervention and those in the control group will perform a post-test at the end of their clinical internship.

## Assignment of interventions: blinding

### Who will be blinded

Participants in intervention group and in control group will be selected from two different medical schools respectively. These medical schools organize also their clinical internships in several hospitals. Therefore, participants will remain unaware of whether they are included in the intervention or control group. Teachers and other clinical internship supervisors will not be informed of the group to which each participant belongs because the intervention will be carried out by the research team directly. The evaluation of the intervention and the analysis of the data will be done by the research team.

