##### Listening sessions

Two listening sessions of these digital recordings will be held in an FMBS classroom. Each session will be held for one hour. Each session will be organized in 3 parts: 10 min for the introduction of the activity and the presentation of tools; 40 min for listening during which each participant will have access to the 5 selected digital audio recordings of heart sounds and 10 min for feedback (collection of participants’ opinions and impressions). These recordings will be played back in a loop (series of 5) to the participants using a computer connected to loudspeakers and the Audacity© software. Four series of 10 min will be made. During these series, each recording will be broadcast for 2 min, for a total of 10 min per serie. The first series will be commented by the supervisor to help participants to identify auscultatory anomalies.

A multimedia package containing the additional lectures and the 5 digital audio recordings will be designed and made available to each participant in the intervention group at the end of the second listening session. Participants will be recommended to use this support to independently conduct similar listening sessions as often as they wish. SMS reminders will be sent to participants to encourage them to use this support.

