### Evaluation of knowledge and skills

Two evaluations (pre-test and post-test) will be organized during this study in the two groups. Each assessment will consist of two parts: a knowledge (theoretical) assessment based on multiple-choice questions and a skills (practical) assessment based on a test to recognize cardiac sounds from the audio files.

The first evaluation (pre-test, see additional file 1) will take place at the beginning of the study, directly after the recruitment of participants. The knowledge (theoretical) assessment will aim to evaluate participants’ basic knowledge and will be made on the basis of a form consisting of 15 multiple-choice questions (1 point per correct answer) validated by a scientific committee. These questions will focus on the basic anatomy and physiology of the heart, as well as the technique and semiological aspects of cardiac auscultation. The skills (practical) assessment will aim to assess the participants’ ability to recognize characteristics of cardiac sounds from audio recordings. Information on the locations of cardiac sound recording sites will be provided to participants. Participants will be invited to listen to these cardiac sound recordings using a computer connected to a loudspeaker. The five digital audio recordings selected (one normal and four pathological) will be numbered from 1 to 5. The reading sequence will be random (using a randomization tool). Each recording will be played and listened for one minute and two additional minutes will be allowed for reflection on each recording and for writing the response. Dimensions assessed will be the normal or pathological nature of a cardiac sound, timing and description of the abnormality if it is present. Each correct answer will give one point, for a total of five points.

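### The protocol claims participants are blinded by recruiting the arms in different schools, but that separation does not mask them, and no masking is described for the team that evaluates and analyses.

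*Protocol article*

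**What the plan says.** The protocol article, Who will be blinded, makes three statements.

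- Students: since the arms are recruited in two schools whose internships run in several hospitals, "participants will remain unaware of whether they are included in the intervention or control group".
- Supervisors: "Teachers and other clinical internship supervisors will not be informed of the group to which each participant belongs", with the reason that the research team itself carries out the intervention.
- Assessment: "The evaluation of the intervention and the analysis of the data will be done by the research team".

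Sequence generation fixes how the arms are formed: "participants in the control group will be selected only at HIMT while participants in the intervention group will be selected at FMBS". The purpose given there is to prevent communication between the groups.

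The arms differ in what students visibly receive. Under Listening sessions, "Two listening sessions of these digital recordings will be held in an FMBS classroom", and a package of lectures and recordings is "made available to each participant in the intervention group at the end of the second listening session". Under Implementation, "Participants in the intervention group will receive additional SMS reminders to encourage them to participate in the supervised listening sessions". Evaluation of knowledge and skills assigns a different satisfaction form to each arm. For the skills test, it lists among the assessed dimensions the "timing and description of the abnormality if it is present".

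**The concern.** A report that repeats the blinding sentence would claim a safeguard the trial does not have, and readers would underrate the risk of bias. Two kinds of outcome are at stake.

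- Skills progression, and total progression through it, may depend on a marker's judgement of how a sound was described. If the marker knows the school, expectation can tip borderline answers.
- Satisfaction is self-reported by students who know what they were given.

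The choice between a t-test and a non-parametric test, and the handling of exclusions, also lie with a team for which no masking is described.

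**Working it through.** No figure in the protocol is at issue, so the check sets the passages side by side.

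**1. Does the reason given support the claim?** Who will be blinded infers unawareness from the two schools. Sequence generation gives the separation a different purpose, the prevention of contact between arms. Separation can serve that purpose. It also makes arm and school the same thing: HIMT is control and FMBS is intervention. It hides nothing from a student about what that student receives.

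**2. What can each group know?**

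| Group | What the article shows | Consequence |
|---|---|---|
| Intervention students | Two one-hour supervised sessions, a take-home package, extra SMS, their own satisfaction form | They know they receive the added activity |
| Control students | Additional lectures, internship, SMS and calls; a distant school | They may not know what the other school receives |
| Internship supervisors | Not told the group; internships are arranged by school, in hospitals that school accredits | They can infer the arm if they know the school and the design |
| Research team | Recruits, allocates, delivers, collects, evaluates, analyses (Who will be blinded; Composition of the coordinating center and trial steering committee) | No masking step is described |

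The participant claim fails on the first row alone.

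**3. Which outcomes can marking reach?** From Evaluation of knowledge and skills and Outcomes:

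- Knowledge (primary): 15 multiple-choice questions, one point per correct answer. There is little room for marker judgement.
- Skills: five recordings, one point each, range 0 to 5. Nature, timing and description are assessed for a single point per recording, so a partly right answer may call for judgement.
- Total: 15 + 5 = 20 points, so the skills items are 5/20 = 25% of the score.
- Satisfaction: a self-completed form, which marking does not affect.

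**4. Can the bias be sized?** Progression is post-test minus pre-test. Let L be the mean number of points gained through lenient marking. The bias in the difference between arms is

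(L post − L pre, intervention) − (L post − L pre, control).

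Leniency towards one school that is equal at both tests cancels. Bias arises only if leniency changes between tests and does so differently by school. The documents give no value for any of the four terms, so the direction of the risk can be named but not its size.

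**The case against.** The strongest reply is that this is one badly worded sentence in a condensed article. The article does not say who marks the sheets or that they are marked with the school visible; sheet coding may be set out in a fuller document. The skills items are scored right or wrong at one point each, and whether the description is free text or a tick-box depends on additional files that are not shown. Supervisors are said only not to be informed, and they score no outcome. Control students may indeed be unaware of their status. The primary outcome is barely touched.

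Much of this stands, and it limits the point. A reader might infer that no masking of anyone is possible. The documents do not support that: for supervisors the claim is weaker than blinding, and control students may not know the contrast. A reader might also infer that unmasked marking is an established fact. It is only a reasonable inference, because the section on blinding assigns evaluation to the team that delivers the intervention and mentions no masking for it. Nor can the content of the information sheet be used as evidence, since it is not shown.

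The reply does not rescue the sentence on participants. That is a positive statement contradicted by the article's own description of the intervention, not a detail left to another document.

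**Conclusion.** The point holds in limited form. The claim that participants are unaware of their arm is wrong for intervention students and should be withdrawn. Effective supervisor blinding should not be claimed either. With no masking described for the evaluating team, skills progression and the quarter of the total score that comes from skills are open to assessor bias. That rests on two assumptions: that team members who know the school do the marking, and that scoring the descriptions involves some judgement.

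The effect of marking on the multiple-choice primary outcome is small. The size of any bias in the other outcomes cannot be derived from the documents, and no numerical estimate should be attached to it. Students' knowledge of their arm may also influence their satisfaction ratings or effort. Masked marking cannot remove that, which is a further reason to describe the study accurately.

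**What to change.** 1. Replace the participant-blinding sentence with a statement that the study is open-label for students and trainers. Say of supervisors only that they are not told the group, without claiming that they are blinded.
2. Have existing team members, preferably those not running the listening sessions, mark answer sheets that carry only a code. Hide school and arm, and mix the two schools' sheets within each test. Hiding pre- or post-test status is not needed and would be difficult, because the question order differs between the two forms.
3. Mark against an answer key fixed before the pre-test, including what counts as a correct timing and description.
4. Release the code list only after the planned double data entry is locked, and run the analysis on arms labelled A and B. Exclusions for missed listening sessions apply to the intervention arm only and would reveal the labels, so apply them before the data reach the analyst.
5. Report satisfaction as an unblinded, self-reported outcome.

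The cost is a revised paragraph and a little extra work coding and mixing the sheets. No additional data or staff are needed. The gain falls on skills and total progression; the primary outcome and satisfaction benefit little from masked marking.
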